#### HbA1c tests

Diabetes is an exclusion criterion (based on HbA1c at screening > 6.5%). However, after screening, annual HbA1c tests are performed until conception and test results shared with the participants’ providers. This is expected to minimize early clinical screenings for pre-existing DM; however, any participant receiving an early (< 24 weeks’ gestation) clinical diagnosis of GDM is included in the analysis.

#### Maternal insulin resistance/physiologic parameters

Maternal fasting glucose, insulin, homeostatic model assessment of insulin resistance (HOMA-IR), leptin, TNF-alpha, C-reactive protein, adiponectin, and lipids are measured by trained staff at each research site, following the established protocols. Blood draws are scheduled 12–24 h after the most recent bout of exercise and after an overnight fast. HOMA-IR is used to estimate insulin resistance. Systolic and diastolic blood pressure are measured using a standard mercury manometer and appropriate size cuffs with participants in the sitting position with both feet on the ground. After resting for 5 min, the average of two measurements is recorded, with a 1–2 min interval between measures.

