### Objectives {7}

The Gestational Diabetes Prevention/Prevención de la Diabetes Gestacional is a two-site randomized clinical trial testing the efficacy of a pre-pregnancy lifestyle intervention to reduce GDM recurrence in women with overweight and obesity. The trial is following the CONSORT guidelines [103]. The primary hypothesis is that the recurrence of GDM will be reduced among participants assigned to pre-pregnancy lifestyle intervention vs. educational control group. Test for GDM will be conducted at 24 to 28 weeks’ gestation. Secondary hypotheses are that the pre-pregnancy lifestyle intervention (vs. educational control group) will result in improved maternal fasting glucose and biomarkers of insulin resistance (insulin, leptin, TNF-alpha, C-reactive protein, and adiponectin) and CVD risk (lipids and blood pressure) assessed before pregnancy, after 16 weeks of intervention, and at 26 weeks’ gestation. The pre-pregnancy lifestyle intervention (vs. educational control group) is expected to reduce adverse perinatal health outcomes for mothers (gestational hypertension, preeclampsia, preterm delivery, excessive gestational weight gain, induction of labor, cesarean delivery) and neonates (admission to the neonatal nursery, hyperbilirubinemia, birth trauma, weight for length *z*-scores ≥ 95% at birth and 6 weeks). Also, the pre-pregnancy lifestyle intervention (vs. educational control group) is hypothesized to result in greater pre-pregnancy weight loss and improvements in diet (calories, % fat, fast food) and physical activity (minutes of moderate activity). In exploratory mediator analyses, treatment-related changes in pre-pregnancy weight, eating, and activity are expected to be related to improvements in maternal physiology and reduced odds of GDM recurrence.

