### Outcomes {12}

#### Primary outcome

The study’s primary outcome is GDM diagnosis in the next pregnancy. The 2-step approach of diagnosing GDM is done at 24–28 weeks’ gestation and involves participants receiving as part of standard care a 50-g oral glucose solution followed by a 1-h venous glucose determination. Participants meeting or exceeding the 1-h screening criteria (a cutoff for an abnormal 1-h screen of ≥ 130 mg/dL) are then referred to the study for completion of the 100-g, 3-h diagnostic oral glucose tolerance test (OGTT). Positive diagnosis of GDM is based on the Carpenter and Coustan criteria [108] based on 2 abnormal values on the 3-h OGTT that includes a fasting value of > 95 mg/dL, 1 h > 180 mg/dL, 2 h > 155 mg/dL, 3 h > 140 mg/dL. The results of the study’s 100-g OGTT are immediately shared with the participants’ medical providers who interpret and inform patients of GDM screening results. If the study measured 100-g, 3-h diagnostic OGTT is not obtained, provider assessments done in standard care that are based on acceptable diagnostic methods (Table 2) are used to diagnose GDM. Final determination of GDM diagnosis is done by an independent evaluation of records from the study’s Ob/Gyn physician-researchers who are masked to the randomized group.

**Table 2 Tab2:** Diagnostic criteria for GDM in Gestational Diabetes Prevention/Prevención de la Diabetes Gestacional

1.	3-h 100 g OGTT performed at ≥ 20 weeks’ gestation in which 2 or more values exceed the criteria as follows: fasting ≥ 95 mg/dL; 1 h ≥ 180 mg/dL; 2 h ≥ 155 mg/dL or 3 h ≥ 140 mg/dL [108]
2.	75 g OGTT performed at ≥ 20 weeks’ gestation and 1 or more values exceed (fasting ≥ 92, 1 h ≥ 180; 2 h ≥ 153) [109]
3.	1-h 50 g test performed at any time during pregnancy with a value ≥ of 200 mg/dL
4.	Fasting glucose value prior to 20 weeks’ gestation ≥ 92 mg/dL and < 125 mg/dL and clinic treats the patient for GDM with medication or insulin
5.	HbA1c conducted anytime during pregnancy with a value ≥ of 5.7% and the clinic treats the patient for GDM with medication or insulin

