#### Maternal/infant consequences of GDM

Chart abstractions are conducted by trained research staff to determine whether the intervention results in fewer adverse maternal and neonatal health outcomes. Consistent with prior research, rates of inadequate and excessive GWG are computed based on the National Academy of Medicine guidelines [118], using measured pre-pregnancy and last clinic visit weights. Other maternal adverse outcomes clinically defined based on chart abstractions include gestational hypertension, preeclampsia, cesarean delivery, labor induction, and delivery < 37.0 weeks’ gestation. Adverse outcomes among infants include birth weight greater than 4000 g, large size for gestational age (defined as birth weight above the 90th percentile), and small size for gestational age (birth weight below the 10th percentile) [144]. A composite measure of serious perinatal complications is defined as one or more of the following: death (stillbirth or neonatal death), hypoglycemia, hyperbilirubinemia, neonatal hyperinsulinemia, shoulder dystocia/birth trauma (brachial plexus palsy or clavicular, humeral, or skull fracture), admission to the neonatal intensive care unit (NICU), and respiratory distress syndrome [13, 145]. An additional composite morbidity outcome is computed based on prior research in women with obesity that includes at least one of the following: cesarean delivery, hypertensive disorders of pregnancy (HDP), birth weight ≥ 4000 g, birth weight < 2500 g, or NICU admission [146]. In women diagnosed with GDM, prescribed treatments are examined to explore whether the intervention impacted the intensity of treatment/severity of GDM.

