## Statistical methods

### Statistical methods for primary and secondary outcomes {20a}

A multiple logistic regression analysis will be used to examine the effect of the treatment group on the proportion of women who develop GDM. The model will include site and covariates to adjust for pre-randomization variables that may relate to the outcome, including parity, age, education, income, smoking, race/ethnicity, BMI, and time since last pregnancy. The effects of the pre-pregnancy weight loss intervention on weight, eating, activity, and physiologic outcomes will be examined using a linear mixed model with fixed effects for treatment condition (the between-groups factor), time (baseline, 16 weeks, 26 weeks’ gestation), site, and baseline covariates. Linear regression and logistic regression analyses will be performed to address the possible effects of the intervention on cases of excessive GWG, gestational hypertension, cesarean delivery, and large for gestational age at birth and 6 weeks, with site and baseline covariates entered in the models. A multiple linear regression analysis will also be used to examine the effect of the treatment group on composite scores of adverse maternal/neonatal outcomes, and logistic regressions will be used to examine separate effects on offspring obesity and odds of exceeding the National Academy of Science guidelines, including the same covariates described above.

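### The analysis of fasting glucose, insulin and HOMA-IR at 26 weeks' gestation makes no exception for women already on GDM medication or insulin, so values drawn under exogenous insulin would count as measures of insulin resistance

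*Protocol article*

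**What the plan says.** Objectives {7} makes maternal fasting glucose and markers of insulin resistance, insulin among them, secondary outcomes "assessed before pregnancy, after 16 weeks of intervention, and at 26 weeks’ gestation". The outcome section on maternal insulin resistance adds HOMA-IR: "HOMA-IR is used to estimate insulin resistance". The only sampling conditions there concern exercise and fasting: "Blood draws are scheduled 12–24 h after the most recent bout of exercise and after an overnight fast". Medication is not mentioned.

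Statistical methods {20a} analyses the physiologic outcomes with a "linear mixed model with fixed effects for treatment condition (the between-groups factor), time (baseline, 16 weeks, 26 weeks’ gestation), site, and baseline covariates". The missing-data section {20c} adds that mixed models may use every existing value.

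On early diagnoses, the section on HbA1c tests says that "any participant receiving an early (< 24 weeks’ gestation) clinical diagnosis of GDM is included in the analysis". Two of the five routes in Table 2 require drug treatment. Item 4, which closes by naming insulin as the alternative, is "Fasting glucose value prior to 20 weeks’ gestation ≥ 92 mg/dL and < 125 mg/dL and clinic treats the patient for GDM with medication or". Item 5 is "HbA1c conducted anytime during pregnancy with a value ≥ of 5.7% and the clinic treats the patient for GDM with medication or insulin". Concomitant care {11d} is unrestricted. Table 1 excludes metformin and similar drugs at entry, so baseline values are drug-free.

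GDM treatment data are to be used for one purpose: "In women diagnosed with GDM, prescribed treatments are examined to explore whether the intervention impacted the intensity of treatment/severity of GDM". They are not linked to the 26-week biomarkers.

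**The concern.** A woman diagnosed through Table 2 item 4, or through item 5 early in pregnancy, can be on medication or insulin before her 26-week blood draw. Two separate problems follow.

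The first is validity. HOMA-IR is built from fasting glucose and fasting insulin and presumes that the insulin is the woman's own. This is a property of the index, not a statement in the article. Under exogenous insulin, neither the measured insulin nor HOMA-IR estimates resistance. Depending on the assay, the error can go either way.

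The second is attenuation of the glucose contrast. Treatment lowers fasting glucose, and if the intervention prevents GDM, more control women than intervention women are treated at the draw. The difference then shrinks when the intervention works. A weak glucose result beside a positive GDM result could be misread as absence of the metabolic effect that the article proposes under Potential mechanisms.

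**Working it through.** **The plan's own figures.** Sample size {14}: 252 × 0.70 = 176.4, so 176 pregnancies and 88 per arm. GDM rates are 60% (53/88) in control and 38% (33/88) in intervention, with stated power of at least 81.98%. With a two-sided 5% level (assumed, as none is stated), the usual two-proportion formula gives 83.7% and an exact Fisher calculation 81.8%. The figure reproduces, and this point disputes no number in the plan. The power of over 80% claimed for the physiologic outcomes cannot be rebuilt, because no effect size or standard deviation is given.

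**Imbalance in treated women.** Let *f* be the share of GDM cases drug-treated before the 26-week draw, taken as equal in both arms. Treated shares are 0.60*f* and 0.38*f*, a ratio of 0.60/0.38 = 1.58. *f* is not in the documents; 5–30% is assumed.

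**Shift in the glucose contrast.** Let *D* be the fall in fasting glucose due to treatment, assumed 5–15 mg/dL. Then

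shift = (0.60 − 0.38) × *f* × *D* = 0.22 × *f* × *D*, toward no difference.

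Lowest corner: 0.22 × 0.05 × 5 = 0.055 mg/dL. Highest corner: 0.22 × 0.30 × 15 = 0.99 mg/dL.

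**Effect on power.** Take an outcome with exactly 80% power at 88 per arm. The detectable difference is (1.960 + 0.842) × √(2/88) = 0.42 SD. Let *D* be 0.5–1.5 SD, which matches 5–15 mg/dL only if the SD is 10 mg/dL (assumed). Power is recomputed at 0.42 − 0.22 × *f* × *D*.

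| *f* | Treated, control vs intervention (of 88) | Shift, mg/dL (*D* = 5 to 15) | Power (*D* = 0.5 to 1.5 SD) |
|---|---|---|---|
| 5% | 2.6 vs 1.7 | 0.055 to 0.165 | 79% to 77% |
| 10% | 5.3 vs 3.3 | 0.11 to 0.33 | 78% to 73% |
| 20% | 10.6 vs 6.7 | 0.22 to 0.66 | 76% to 66% |
| 30% | 15.8 vs 10.0 | 0.33 to 0.99 | 73% to 57% |

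**Insulin and HOMA-IR.** No comparable sum applies, because the sign of the error is not fixed. The argument is one of validity: the article names the index without exception, two diagnostic routes presuppose medication or insulin, and nothing stated removes those draws.

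**The case against.** The strongest objection is that this is an inference from silence. No sentence says that values on treatment are to be handled as if untreated, and handling of treatment started after randomisation could sit in an analysis plan that is not shown. That is fair as to intent. It does not dispose of the point, because the article itself fixes the index and the model for the 26-week values without an exception.

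Second, few women may be affected. Items 4 and 5 apply only when the study's 3-hour OGTT is not obtained, and item 5 can be met at any time in pregnancy. In the main pathway, screen-positive women come to the study for the diagnostic test, and Table 3 puts that test and the glucose and insulin samples at the same 26-week time point. These women are sampled at about the time of diagnosis. The article also does not say which analysis its inclusion of early diagnoses refers to. All this stands and confines the problem mainly to early, drug-treated diagnoses, whose number is not given.

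Third, analysing glucose as observed whatever treatment was given is a legitimate treatment-policy comparison and fits the intention-to-treat principle in {20c}. This stands too, and it is why imputing untreated glucose should not become the main analysis.

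A reader might infer that the control arm's worst values are treated away. The documents do not support that. Treated women occur in both arms, an imbalance is expected only if the intervention works, and the direction toward no difference holds for glucose only.

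A reader might also reach a larger shift by supposing that 10–30% of all control women are treated, half that share in the intervention arm, and a fall of 8–15 mg/dL: (0.10 − 0.05) × 8 = 0.4 to (0.30 − 0.15) × 15 = 2.25 mg/dL. The protocol's rates imply a ratio of 0.38/0.60 = 0.63 rather than one half, which gives 0.29 to 1.65 mg/dL. Treating 10–30% of all controls also means treating 17–50% of control GDM cases (0.10/0.60 to 0.30/0.60), for which the documents offer no support.

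**Conclusion.** The point holds in limited form. As written, the plan lets insulin and HOMA-IR values drawn under exogenous insulin into a secondary outcome that they cannot measure. That part needs no assumption about arm imbalance; how much it matters depends on how many such women there are.

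For fasting glucose, the expected shift is about 0.05–1.0 mg/dL toward no difference. This rests on the protocol's 60% vs 38%, on *f* of 5–30% and *D* of 5–15 mg/dL, and on both being equal across arms. If the intervention also makes the remaining cases milder, the imbalance is larger; if it mainly prevents mild cases, it is smaller. The shift is negligible if early drug treatment is rare, and material only near the top of the range. If the intervention has no effect on GDM, no imbalance is expected under these assumptions, so this is a loss of sensitivity and not a source of false positive glucose findings.

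The primary outcome and the 16-week pre-pregnancy comparison are not affected. Nor are the candidate mediators, which are changes before pregnancy.

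**What to change.** - Record for each woman whether glucose-lowering medication or insulin had been started before the 26-week draw, with the start date.
- Treat insulin and HOMA-IR values drawn under exogenous insulin as missing, handle them with the missing-data methods already described in {20c}, and report their number by arm.
- Keep the as-observed fasting glucose comparison as the main analysis and label it treatment-policy. Add a sensitivity analysis that treats glucose values on medication as treatment-affected. A pre-treatment fasting value will not always exist to bound such values, for example when the diagnosis rests on the 50-g screen or HbA1c.

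The cost is some analysis wording and one added item in the chart abstraction, since the article mentions prescribed treatments but not when they started. No visits or samples are added. The downside is that a few insulin and HOMA-IR values are lost after randomisation, mostly from severe cases, so the missingness is unlikely to be ignorable. Those results should be read together with the sensitivity analyses for missing data that {20c} already foresees.

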#### Maternal anthropometrics

Weight is measured to the nearest 0.1 kg using calibrated standard digital scales. Two measures are completed with participants measured in light clothing (without shoes). Scale calibration is checked weekly with known weights. Standing height is measured twice in patients without shoes in millimeters with wall-mounted Harpenden stadiometers. Given the emerging evidence of a relationship between abdominal fat and GDM [125], waist circumference is measured over bare skin or underwear using a tape measure and following standardized protocols.

*Lifestyle behaviors* are measured to examine the treatment effects and relationships with maternal physiology and GDM recurrence. Physical activity is measured for 7 days using the actigraph accelerometer (MTI, Inc.) which provides minutes and time spent in light, moderate, and vigorous activity over a period of days or weeks [126–128]. TV and sedentary behavior are assessed by pre-established questionnaires [129, 130]. Dietary intake is measured using 24-h recalls on 2 random days over a week [131–135] and completed in an interview format using the NCI Automated Self-Administered 24 h recall (ASA24 http://riskfactor.cancer.gov/tools/instruments/asa24.html). The primary variables of interest are calories, protein, carbohydrates, and fat; consumption of sugar-sweetened beverages; and fast food. Fast food consumption is also assessed based on validated self-report questions [136]. Weight control practices are assessed using the validated Weight Control Strategies Scale [137]. A supplemental brief assessment [138] is administered to assess the frequency of self-weighing, self-monitoring, and meal patterns. Given the association between perceptions of risk and adoption of lifestyle changes, the perceived risk of GDM recurrence is measured at baseline and after 4 months using the Risk Perception Survey modified for GDM [139]. The Center for Epidemiologic Studies Depression (CES-D) screener [140] is used to examine the levels of depressive symptoms; the 14-item Perceived Stress Scale is used to measure the levels of stress, which is a predictor of GDM [141]; and the Eating Inventory [142] assesses the three dimensions of dietary restraint, including cognitive restraint, disinhibition, and hunger. The General Sleep Disturbance Scale (GSDS) is used for a subjective measure of sleep disturbance which has been related to the risk of GDM [143].

#### Maternal/infant consequences of GDM

Chart abstractions are conducted by trained research staff to determine whether the intervention results in fewer adverse maternal and neonatal health outcomes. Consistent with prior research, rates of inadequate and excessive GWG are computed based on the National Academy of Medicine guidelines [118], using measured pre-pregnancy and last clinic visit weights. Other maternal adverse outcomes clinically defined based on chart abstractions include gestational hypertension, preeclampsia, cesarean delivery, labor induction, and delivery < 37.0 weeks’ gestation. Adverse outcomes among infants include birth weight greater than 4000 g, large size for gestational age (defined as birth weight above the 90th percentile), and small size for gestational age (birth weight below the 10th percentile) [144]. A composite measure of serious perinatal complications is defined as one or more of the following: death (stillbirth or neonatal death), hypoglycemia, hyperbilirubinemia, neonatal hyperinsulinemia, shoulder dystocia/birth trauma (brachial plexus palsy or clavicular, humeral, or skull fracture), admission to the neonatal intensive care unit (NICU), and respiratory distress syndrome [13, 145]. An additional composite morbidity outcome is computed based on prior research in women with obesity that includes at least one of the following: cesarean delivery, hypertensive disorders of pregnancy (HDP), birth weight ≥ 4000 g, birth weight < 2500 g, or NICU admission [146]. In women diagnosed with GDM, prescribed treatments are examined to explore whether the intervention impacted the intensity of treatment/severity of GDM.

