### Relevant concomitant care permitted or prohibited during the trial {11d}

During the trial, participants are not restricted from receiving concomitant care and/or interventions.

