#### Infant measures

At 6 weeks, infant length, weight, and skinfold thickness measurements are performed by trained staff using standardized procedures. BMI *z*-scores are calculated using the WHO Child Growth Standards for age and sex [147]. A *z*-score of > 1 will be used to define at risk for obesity.

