**Lifestyle behaviors**					
Physical activity	X	X	–	X	–
Dietary intake	X	X	–	X	–
Behavioral and psychosocial	X	X	brief	X	–
**Infant weight, length**	–	–	–	–	X
**Maternal/infant complications**	–	–	–	–	X
**Process measures**	–	X	X	–	–

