### Sample size {14}

Power calculations assume a 60% GDM recurrence rate in women with overweight or obesity [19, 57, 58]. With a target sample size of 252 participants and assumed ≥ 70% pregnancy rate [151, 152] and 30% lost to follow-up or not pregnant before conception, ≥ 176 pregnant participants (≥ 88 in each group) would provide adequate statistical power (≥ 81.98%) to detect intervention effects on the proportions developing recurrent GDM [83, 153], taking into account estimations of site-specific clustering effects and effect modifiers (i.e., weight status, ethnicity, parity) of GDM recurrence [24, 57]. Under this scenario, the minimum detectable effect size (odds ratio) would be 0.43, and proportions with GDM in educational control and intervention groups respectively would be 60% (*n* = 53/88) and 38% (*n* = 33/88). For secondary aims, 88 pregnancies in each group would yield > 80% power to detect effects equal to or smaller than those reported in prior work testing effects of lifestyle interventions on reductions in glucose, triglycerides, CRP [154], insulin, leptin [155], adiponectin [156], and blood pressure [157], taking into account estimations of site-specific clustering effects and effect modifiers (i.e., weight status, ethnicity, parity) of insulin resistance [158], and CVD risk factors [159, 160]. For secondary aims examining effects of the intervention on prenatal and perinatal complications, the study would have > 80% power to detect moderate effect sizes [161]. For the fourth aim examining the effects of the intervention on pre-pregnancy weight losses and improvements in eating (calories, macronutrient balance, fast food) and activity, 88 participants in each group would yield > 90% power to detect effects reported in prior work testing effects of lifestyle interventions on reductions in weight [157] and behavioral variables [162, 163]. For exploratory mediator analyses, > 80% power is achieved to detect > 21% increase in the mediated odds of GDM per kilogram difference in pre-pregnancy weight loss (equivalent to a mediated slope in a logistic model of > 0.189).

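### The serious perinatal composite counts chart-found hypoglycemia and hyperinsulinemia; if clinics test newborns of GDM mothers more often, detection would depend on the trial's primary outcome

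*Protocol article*

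**What the plan says.** All references are to the protocol article.

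- **Definition.** Under Outcomes {12}, Maternal/infant consequences of GDM: "A composite measure of serious perinatal complications is defined as one or more of the following". The list includes "death (stillbirth or neonatal death), hypoglycemia, hyperbilirubinemia, neonatal hyperinsulinemia, shoulder dystocia/birth trauma", and goes on to NICU admission and respiratory distress syndrome.
- **Source.** The same section states: "Chart abstractions are conducted by trained research staff to determine whether the intervention results in fewer adverse maternal and neonatal health outcomes".
- **Study measurements on the infant.** Under Infant measures, at 6 weeks, "infant length, weight, and skinfold thickness measurements are performed by trained staff using standardized procedures". Table 3 has an infant row "Infant weight, length" and a row for complications, both at the 6-week postpartum visit. Neither place mentions a newborn glucose or insulin assay.
- **Who knows the GDM result.** Under Primary outcome, the study's glucose tolerance results go at once to the "medical providers who interpret and inform patients of GDM screening results".
- **Clinical care.** Under {11d}, "participants are not restricted from receiving concomitant care and/or interventions".
- **Analysis.** Statistical methods {20a} compares composites between arms with site and baseline covariates. It does not address how intensively newborns were tested.

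**The concern.** Hypoglycemia and neonatal hyperinsulinemia are laboratory findings. As the outcome is described, they can be counted only where a clinician chose to test the newborn. Clinicians know whether the mother had GDM, and the Background says that GDM exposure is associated with neonatal hypoglycemia, so a known GDM label gives them a reason to look.

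If they act on it, the chance that an event is found depends on the variable the intervention is meant to change. The arms would then differ in ascertainment of the same harm. Masked research assistants cannot correct this, because an event that was never tested for is not in the chart. A trial that lowered GDM could report fewer serious perinatal complications partly because fewer newborns were tested, and the plan as described would not show how large that part was.

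**Working it through.** **Inputs from the protocol article (Sample size {14}).** GDM 60% (53/88) in control and 38% (33/88) in intervention, with 88 pregnancies per arm.

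**The plan's own figure.** No figure is given for this composite beyond a general statement of more than 80% power for moderate effects. For the primary outcome, a pooled two-proportion test with two-sided alpha 0.05 (assumed, since alpha is not stated) gives:

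- mean proportion 0.49; null SE = √(2 × 0.49 × 0.51 / 88) = 0.0754
- alternative SE = √((0.60 × 0.40 + 0.38 × 0.62) / 88) = 0.0735
- z = (0.22 − 1.96 × 0.0754) / 0.0735 ≈ 0.98, so power ≈ 83.7%

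The plan states at least 81.98% after allowing for clustering and effect modifiers. The 60% versus 38% scenario is therefore a fair basis.

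**Assumptions not in the documents.** Every newborn of a GDM mother is tested. A share t of other newborns is tested, regardless of whether they are hypoglycemic. True hypoglycemia has the same rate h in both arms and is unrelated to GDM, so any difference is pure artefact.

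**Step 1: share of hypoglycemia detected.**

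- Control: 0.60 + 0.40t
- Intervention: 0.38 + 0.62t
- Difference: 0.22 × (1 − t)

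| t | Control | Intervention | Difference | Spurious risk ratio |
|---|---|---|---|---|
| 0.2 | 0.680 | 0.504 | 0.176 | 0.74 |
| 0.5 | 0.800 | 0.690 | 0.110 | 0.86 |
| 0.7 | 0.880 | 0.814 | 0.066 | 0.93 |
| 1.0 | 1.000 | 1.000 | 0 | 1.00 |

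**Step 2: the composite.** Let o be the proportion with some other component, independent of hypoglycemia. The composite rate is 1 − (1 − o)(1 − h × detected share), so the spurious difference is (1 − o) × h × 0.22 × (1 − t). With assumed h of 10% to 30% and o of 15% to 25%:

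- t = 0.2: from 0.75 × 0.10 × 0.176 = 1.3 points to 0.85 × 0.30 × 0.176 = 4.5 points
- t = 0.5: from 0.75 × 0.10 × 0.110 = 0.8 points to 0.85 × 0.30 × 0.110 = 2.8 points

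**Step 3: overlap.** If a share v of hypoglycemic newborns meets the composite anyway, for example through NICU admission, the difference becomes (1 − v) × h × 0.22 × (1 − t). With v = 0.5 and t = 0.2 it is 0.9 to 2.6 points (0.5 × 0.10 × 0.176 and 0.5 × 0.30 × 0.176). With complete overlap it is zero.

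**Step 4: direction.** With equal GDM rates the ratio is 1.00 for any t. The Background cites a Finnish preconception trial with GDM of 60% in intervention and 54% in control. At t = 0.5 those rates give (0.60 + 0.40 × 0.5) / (0.54 + 0.46 × 0.5) = 0.80 / 0.77 = 1.04, so the artefact then works against the intervention.

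**Step 5: effect on a test.** With 88 per arm, h and o each 10% to 30% and t from 0.5 down to 0, the artefact alone gives a rejection probability in favour of the intervention of about 3% to 15%, against a nominal 2.5%.

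**The case against.** A reader might infer that newborn testing does follow the mother's GDM label and that the comparison therefore favours the intervention. The documents support neither step. No section says who orders newborn tests or how often. The direction needs GDM to be lower in the intervention arm, which is the hypothesis under test.

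The calculation also leans towards a large artefact:

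- If clinics test the non-GDM newborns most likely to be hypoglycemic, more than a share t of their events is found and the gap narrows.
- If only 80% of GDM newborns are tested, then at t = 0.5 detection is 0.60 × 0.8 + 0.40 × 0.5 = 0.680 versus 0.38 × 0.8 + 0.62 × 0.5 = 0.614, a ratio of 0.90 rather than 0.86.
- Given the association stated in the Background, part of any observed difference would be a real benefit of less GDM.

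The plan also has some protection. A second prespecified composite contains no glucose or insulin component. The neonatal outcomes named under Objectives {7} include neither hypoglycemia nor hyperinsulinemia. The composite follows cited work, and the operational definitions may sit in the full protocol. Hyperbilirubinemia and NICU admission also depend on clinicians, so dropping two components does not make the rest fully objective.

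These points make the concern conditional and reduce its size. They also argue against redefining the main composite. Counting only treated hypoglycemia would not help much, because treatment also follows detection. What stands is that the article describes neither uniform newborn testing nor a record of who was tested, so the artefact could be neither ruled out nor measured from what is planned.

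**Conclusion.** The concern holds as a conditional risk of differential ascertainment in one secondary composite. The primary outcome is not affected. The documents establish that the two components come from charts, that no study newborn sample is described, and that clinicians know the GDM result. More frequent testing of newborns of GDM mothers is an assumption.

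Under that assumption, with 60% versus 38% GDM, all GDM newborns tested and no true neonatal effect, the spurious ratio for detected hypoglycemia is about 0.74 to 0.93 for non-GDM testing of 20% to 70%. The spurious composite difference is about 1 to 4.5 points for testing of 20% to 50%, and smaller if components overlap. It vanishes if GDM rates are equal and reverses if GDM is commoner in the intervention arm. This is modest, but enough to blur a neonatal claim, and it is cheap to guard against.

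**What to change.** Keep the literature-based composite as defined, and make three additions:

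1. In the chart abstraction described under Maternal/infant consequences of GDM, record whether newborn glucose (and insulin) was tested, and report the tested share by arm.
2. In Statistical methods {20a}, prespecify as a sensitivity analysis the same composite without hypoglycemia and neonatal hyperinsulinemia, analysed in the same way.
3. State that a neonatal benefit on this composite will be concluded only if the two analyses agree in direction and approximate size.

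The cost is one extra abstraction field and one extra analysis, with no change to newborn care. The sensitivity composite will have fewer events and so less precision. If a true benefit acts mainly through less hypoglycemia, the sensitivity analysis will understate it and the rule in item 3 will be cautious. The tested shares by arm will help the reader judge which explanation is more likely.
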